**Protocol**

This trial protocol has been provided by the authors to give readers additional information about their work.

**Effectiveness of Interferon Beta 1a and Interferon Beta 1b compared to the Usual Therapeutic Regimen to Treat Adults with Moderate to Severe COVID-19**

A single center, open label, randomized, controlled, parallel group, clinical trial

# **PROTOCOL SUMMARY**

**Study Title:**

Effectiveness of Interferon Beta 1a and Interferon Beta 1b compared to the Usual Therapeutic Regimen to Treat Adults with Moderate to Severe COVID-19

**Objectives:**

We will investigate the effectiveness of Interferon Beta 1a, compared to Interferon Beta 1b and the usual therapeutic regimen in COVID-19 in patients that have tested positive and are moderately to severely ill.

**Trial Design:**

This is a single center, open label, randomized, controlled, parallel group, clinical trial that will be conducted at Loghman Hakim hospital in conjunction with Shahid Beheshti University of Medical Sciences.

**Participants:**

Sixty COVID-19 confirmed cases (using the RT-PCR test) will be enrolled in the trial between April 9^th^ to April 14^th^ 2020. Patients will be randomly assigned to the intervention groups or the control group with the following eligibility criteria: ≥ 18 years of age AND (oxygen saturation (SPO2) ≤ 93% OR respiratory rate ≥ 24) AND at least one of the following: Contactless infrared forehead thermometer temperature of ≥37.8°C, cough, sore throat, nasal congestion/drip, myalgia, headache or fatigue on admission, and onset of the symptoms should be acute (Days ≤ 14). Although Hydroxychloroquine will be administered in a single dose, patients with heart problems (prolonged corrected QT (450 milliseconds) or PR intervals, second- or third-degree heart block, and history of arrhythmias including torsade de pointes) will be excluded. Other exclusion criteria include using drugs with potential interaction with Hydroxychloroquine + Lopinavir/Ritonavir, Interferon-β 1a, Interferon-β 1b, pregnant or lactating women, history of alcohol or drug addiction in the past 5 years, blood ALT/AST levels > 5 times the upper limit of normal on laboratory results and refusal to participate.

This study will be undertaken at the Loghman Hakim Hospital, Shahid Beheshti University of Medical Sciences.

**Intervention and Comparator:**

COVID-19 confirmed patients will be randomly assigned to one of three groups, with 20 patients in each. The first group (Arm 1) will receive Hydroxychloroquine + Lopinavir / Ritonavir (Kaletra) + Interferon-β 1a (Recigen), the second group (Arm 2) will be administered Hydroxychloroquine + Lopinavir / Ritonavir (Kaletra) + Interferon-β 1b (Ziferon), and the control group (Arm 3) will be treated by Hydroxychloroquine + Lopinavir / Ritonavir (Kaletra).

**Efficacy Assessments:**

**Primary outcome:**

Time to clinical improvement is our primary outcome measure. This is an improvement of two points on a seven-category ordinal scale (recommended by the World Health Organization: Coronavirus disease (COVID-2019) R&D. Geneva: World Health Organization) or discharge from the hospital, whichever comes first.

**Secondary outcomes:**

Secondary outcomes include mortality from the date of randomization until the last day of the study which will be the day all of the patients have had at least one of the following outcomes: 1) Improvement of two points on a seven-category ordinal scale. 2) Discharge from the hospital 3) Death. If any patient dies, we have reached an important secondary outcome. SpO2 Improvement between the last and first day of hospitalization, using pulse-oximetry. Duration of hospitalization from date of randomization until the date of hospital discharge or date of death from any cause, whichever comes first. Incidence of new mechanical ventilation uses from date of randomization until the last day of the study. Please note that we are trying to add further secondary outcomes and this section of the protocol is still evolving.

**Statistical Methods:**

Statistical analysis will be performed by R version 3.6.1 software. We will use Kaplan–Meier to analyze the time to clinical improvement (compared with a log-rank test). Hazard ratios with 95% confidence intervals will be calculated using the Cox proportional-hazards model in crude and adjusted analysis.

# **INTRODUCTION**

**Background**

As of 1^th^ March, 2020, a cumulative total of 8,116 Coronavirus (COVID-19) cases were detected in China and 11,011 patients out of China. Among Chinese patients, the death was 3,231, or 3.98%. While the number of deaths due to COVID-19, outside China has been reported as 4576 cases. So far in Iran, the COVID19 test of 16169 people has been reported positively and the number of deaths has been 988 individuals, with 6.11% mortality rates (1).

Coronavirus SARS-CoV-2, an enveloped RNA virus, is responsible for severe respiratory illness and viral pneumonia around the world. As COVID-19 is a new pathogen, everyone is assumed to be susceptible and there is no known pre-existing immunity in humans. So, according to epidemiologic reports from china and other countries, it has become a global health emergency (2).

SARS-CoV-2 belongs to the β-coronavirus cluster, as do SARS-CoV and MERS-CoV (3). However, it is not SARS or influenza, it is a novel virus with its own features. Generally, Viral infection in mammalian cells activates the body's innate immune system and interferons (IFNs) play a key role in this event because they activate the innate immune system and also contribute to acquired immunity. There are two types of IFN involved in antiviral activity: Type I is synthesized by most cell types as a direct response to the virus, while type II is produced by immune cells after contact with cells containing antigens. Both type I and type II have antiviral, anti-proliferative, and immune system modulating properties (4). In animal model with SARS-CoV infection, IFN imbalance of type I and inflammatory cells was shown to be the leading cause of fatal pneumonia (5). According to lack of information available on COVID-19, SARS could be a useful model in this regard. Because SARS-CoV-2 resemble to SARS-CoV in structure and nucleotide sequence among other viruses of this family (6), another study found that Coronavirus targets the most important proteins in the IFN signaling pathway to fight the immune system. This study highlighted the main role of the IFN-mediated antivirus in responding to Coronavirus infection (7).

IFN-β 1a is currently used for a variety of diseases, including multiple sclerosis, and has been shown to be effective in several dose-dependent clinical trials. Significantly, IFN-β 1a has a strong antiviral activity have shown in previous studies and also has an acceptable safety profile. In a 2003 study, SARS was treated with human interferons and found that IFN-β was 5 to 10 times more effective than other types of interferons and was the best antiviral drug against SARS-CoV (8).

Due to COVID-19 outbreak, the novel nature, astonishing speed of spreading, severe disease, death and limited data, further studies are required to fill this knowledge gap. So we also aim to examine the therapeutic effect of Interferon Beta 1a, compared to Interferon Beta 1b and the usual therapeutic regimen in COVID-19 in patients that have tested positive and are moderately to severely ill.

Since the recent global outbreak of COVID19, extensive attempts were performed to better understand the new virus and its clinical features. Although lots of clinical trials were conducted, key knowledge gaps remain and so far there is not definitive and effective treatment to manage the disease.

Our study introduces a new therapeutic regimen that reduces mortality rates, length of hospital stay (LOHS) and improves clinical symptoms in patients with COVID-19. So the present therapeutic regimen, as a promising solution, could help health care systems to deal with difficulties caused by the COVID-19 pandemic.

Moreover, to the best of our knowledge, this is the first report, investigating the effectiveness of Interferon Beta 1a, compared to Interferon Beta 1b and the usual therapeutic regimen in COVID-19 confirmed cases.

# **STUDY OBJECTIVES**

**Primary objective**

We will investigate the effectiveness of Interferon Beta 1a, compared to Interferon Beta 1b and the usual therapeutic regimen in COVID-19 in patients that have tested positive and are moderately to severely ill.

**Secondary objectives**

The secondary objectives for this study are:

1. To determine and compare the frequency of side effects in three therapeutic arms
2. To determine and compare the average level of oxygen saturation (Sat O2) in three therapeutic arms.
3. To determine and compare the average respiratory rate (RR) in three therapeutic arms
4. To determine and compare the average length of hospital stay in three therapeutic arms
5. To determine and compare the average length of hospital stay in the intensive care unit (ICU) between three therapeutic arms
6. To determine and compare the frequency of 30-days mortality rates between three therapeutic arms
7. To determine and compare the average time to improve clinical symptoms between three therapeutic arms
8. To determine and compare the average SOFA score in three therapeutic arms
9. To determine and compare the average duration of mechanical ventilation use between three therapeutic arms

**Practical Objective**

To introduce a new therapeutic regimen in order to reduce mortality rates and improve related symptoms in COVID-19 patients.

**Hypothesis**

- The frequency of side effects varies in each of the 3 treatment groups
- The average level of oxygen saturation (Sat O2) varies in each of the 3 treatment groups
- The average respiratory rate (RR) in each of the 3 treatment groups is different
- The average length of hospital stay varies in each of the 3 treatment groups
- The average length of hospital stay in ICU varies in each of the 3 treatment groups
- The frequency of 30-day mortality varies in each of the 3 treatment groups
- The average time until the nasopharyngeal swap test is negative in each of the 3 treatment groups is different
- The average time to clinical improvement in each of the 3 treatment groups is different
- The average SOFA score varies in each of the 3 treatment groups
- The average duration of mechanical ventilation varies in each of 3 treatment groups

# **STUDY DESIGN**

**General**

This is a single center, open label, randomized, controlled, parallel group, clinical trial that will be conducted at Loghman Hakim Medical Education Center in conjunction with Shahid Beheshti University of Medical Sciences.

Eligible patients with confirmed SARS-Cov-2 infections will be randomly assigned in a 1:1:1 ratio to one of the three following therapeutic regiments: 1) IFNβ1a (Recigen) (Subcutaneous injections of 44μg (12,000 IU) on days 1, 3, 6) + Hydroxychloroquine + Lopinavir/Ritonavir (Kaletra) [IFNβ1a group], 2) IFNβ1b (Ziferon) (Subcutaneous injections of 0.25mg (8,000,000 IU) on days 1, 3, 6) + Hydroxychloroquine + Lopinavir/Ritonavir (Kaletra) [IFNβ1b group], and 3) Hydroxychloroquine (Single dose of 400 mg on day 1, orally, in all three arms) + Lopinavir/Ritonavir (Kaletra) (400mg/100 mg twice a day for 10 days, orally, in all three arms) [control group]. All three groups will receive standards of care consisting of the necessary oxygen support, non-invasive, or invasive mechanical ventilation.

Patients will be randomly allocated to three therapeutic arms using permuted, block-randomization to balance the number of patients allocated to each group. The permuted block (three or six patients per block) randomization sequence will be generated, using Package ‘randomizeR’ in R software version 3.6.1. and placed in individual sealed and opaque envelopes by the statistician. The investigator will enroll the patients and only then open envelopes to assign patients to the different treatment groups. This method of allocation concealment will result in minimum selection and confounding biases.

The present research is open-label (no masking) of patients and health care professionals who are undertaking outcome assessment of the primary outcome - time to clinical improvement.

## **Safety Assessments**

Regarding safety concerns, daily monitoring for adverse effects (AEs) and treatment-related AEs, vital signs, and laboratory testing will be carried out. All adverse effects should be recorded and include time, severity, symptoms, and their relation with aforementioned drugs.

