**Secondary Outcomes:**

Secondary outcomes include mortality from the date of randomization until day 21, by which all of the patients will have at least one of the following outcomes: 1) A decline of two steps on the seven-step ordinal scale, 2) Hospital discharge or 3) Death; SpO2 improvement defined as the difference between the last and the first recorded measurement during the hospitalization, using pulse-oximetry; length of stay in the hospital until the date of discharge from hospital or death from any cause, whichsoever came first; incidence of new mechanical ventilation uses from the date of randomization until day 21. Follow-ups of discharged patients will be done utilizing telemedicine visits, online, or over the telephone.

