## **Study Drugs**

- **Hydroxychloroquine:**

400mg bid for first day then 200mg bid for 10 days

- **lopinavir/ritonavir (Kaletra):**

400mg/100mg bid for 10-14 days

For those that could not get orally:

5-ml suspension bid for 10-14 days

- **Interferon beta-1a:**

SC injection 44 micro-gram for 3 days (on days 1,3,6)

- **Interferon beta-1b:**

SC injection 0.25 mg for 3 days (on days 1,3,6)

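### No end of side-effect collection is set; if it stops at discharge, the arm discharged sooner can show fewer side effects with no true difference

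*Protocol*

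**What the plan says.** The first of the Secondary objectives is "To determine and compare the frequency of side effects in three therapeutic arms". The first item under Hypothesis is the matching claim: "The frequency of side effects varies in each of the 3 treatment groups". Neither gives a time window.

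Safety Assessments holds the whole collection rule: "daily monitoring for adverse effects (AEs) and treatment-related AEs, vital signs, and laboratory testing will be carried out", followed by "All adverse effects should be recorded and include time, severity, symptoms, and their relation with aforementioned drugs". No end of collection and no setting is named.

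Secondary Outcomes (under Efficacy Assessments) fixes day 21 for mortality and for ventilation: "incidence of new mechanical ventilation uses from the date of randomization until day 21". It then adds "Follow-ups of discharged patients will be done utilizing telemedicine visits, online, or over the telephone". That sentence has no schedule and does not mention side effects.

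The lopinavir/ritonavir course is given as "400mg/100 mg twice a day for 10 days, orally, in all three arms" in the General section and as "400mg/100mg bid for 10-14 days" under Study Drugs. Nothing ties discharge to the end of the course, and discharge is one of the two ways to reach the primary outcome.

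**The concern.** A proportion of patients with a side effect is comparable between arms only if the arms are watched for the same length of time. Here the watching consists of daily vital signs and laboratory tests at a single hospital, which most naturally ends when the patient goes home. Length of stay would then set the time at risk of being recorded. The protocol itself hypothesises that stay differs by arm, and its Background says that the regimen shortens it.

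If interferon does shorten stay, its recorded side-effect frequency is pulled down relative to control, and a real excess could be masked. If interferon prolongs stay, the distortion reverses. The same applies between the two interferon arms. Events that nobody asked about after discharge cannot be recovered by any later analysis, so the collection window has to be fixed in the protocol.

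**Working it through.** **Step 1. What the planned hazard ratio refers to.** The Statistical Methods section gives 80% power, alpha 0.05 (taken here as two-sided), HR 3.0, 80% reaching the primary outcome and 15% dropout.

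- Events for one interferon-control comparison: (1.960 + 0.842)² / (0.25 × (ln 3)²) = 26.01, so 27.
- Patients: 27 / 0.8 = 33.75, so 34; then 34 / 0.85 = 40 for two arms.
- This gives 20 per arm and 60 in all, as stated.

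The 3.0 is therefore a pairwise assumption about time to improvement or discharge. The protocol gives no hazard ratio for discharge alone, no length of stay and no side-effect rate.

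**Step 2. Assumptions for the illustration (none is in the protocol).** Time to discharge is exponential, 70% of controls are discharged by day 21, and deaths are ignored. The true rate of first side effects is a = 0.05 per day in both arms. Collection stops at discharge or day 21. The discharge hazard ratio is 3.0 or, more mildly, 1.5.

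- Control discharge hazard: h = -ln(0.30) / 21 = 0.0573 per day.
- Interferon: 3 × 0.0573 = 0.172, or 1.5 × 0.0573 = 0.086.
- Mean days observed, (1 - exp(-21h)) / h: control 12.2; interferon 5.7 at HR 3.0 and 9.7 at HR 1.5.

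**Step 3. Recorded proportions.** If events can arise only up to day W, the proportion with an event seen before discharge is a / (a + h) × (1 - exp(-W(a + h))). The true proportion over the same period is 1 - exp(-aW), the same in both arms.

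Worked case, W = 21, HR 3.0:
- Control: 0.05 / 0.1073 × (1 - exp(-21 × 0.1073)) = 0.417.
- Interferon: 0.05 / 0.222 × (1 - exp(-21 × 0.222)) = 0.223.

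| Events arise in | True, both arms | Control, recorded | Interferon, HR 3.0 | Interferon, HR 1.5 |
|---|---|---|---|---|
| days 0-21 | 65% | 42% | 22% | 35% |
| days 0-10 | 39% | 31% | 20% | 27% |
| days 0-6 | 26% | 22% | 17% | 21% |

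From the unrounded values, the interferon-to-control ratio is 0.54, 0.65 and 0.75 at HR 3.0, and 0.83, 0.89 and 0.93 at HR 1.5. It should be 1.0 throughout.

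**Step 4. Sensitivity to the discharge assumption.** With 60% to 80% of controls discharged by day 21, HR 3.0 and events to day 21, the gap runs from 46% vs 27% to 37% vs 18%. A second calibration sets 80% discharged by day 21 across two arms combined at HR 3.0, with true 21-day risks of 30%, 50% or 70%. It gives mean observation of 13.1 vs 6.5 days and a false ratio of 0.52 to 0.58. With the slower arm's hazard unchanged and HR 1.5, the ratio is 0.82 to 0.85.

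**Step 5. Overlap with the oral course.** Under the Step 2 assumptions, the proportion home before day 10 is 1 - exp(-10 × 0.0573) = 44% of controls, and 1 - exp(-10 × 0.172) = 82% of interferon patients at HR 3.0 (58% at HR 1.5). Collection that ended at discharge could thus end while the stated course is still running.

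**The case against.** The strongest reply is that the protocol never confines collection to the hospital. Safety Assessments asks for all adverse effects to be recorded and does not end the record at discharge. The remote follow-up sentence stands alone, and only its place under Secondary Outcomes suggests that it serves the efficacy outcomes. If those contacts pick up side effects, most of the distortion in symptomatic events goes. This stands: in-hospital collection is an inference, and the bias is a risk that depends on it.

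The size is also open to challenge, on four grounds.

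- HR 3.0 covers improvement or discharge. A patient who moves from category V to category III has met the endpoint while still in hospital, so the effect on discharge alone may be smaller.
- The 0.172 per day hazard would send about 64% of interferon patients home within 6 days, 1 - exp(-6 × 0.172), which is hard to credit for patients enrolled with low oxygen saturation or fast breathing.
- Injections fall on days 1, 3 and 6, so reactions to them would be lost less often than late effects. The day 0-6 row of the table shows this: the gap narrows but does not vanish.
- Even a gap near the widest, about 8/20 vs 4/20, gives an uncorrected chi-square of 1.90 (p about 0.17). The likelier harm is a hidden excess, not a formally significant advantage for interferon.

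Finally, the choice between per-patient and per-patient-day reporting can be left to the SAP, and the chi-square sentence in Statistical Methods does not name side effects. That is accepted, and no criticism of the test is made here. It does not answer the missing collection window, which the SAP cannot repair afterwards.

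**Conclusion.** The point holds in conditional form. A between-arm side-effect comparison is planned with no common collection window, and the post-discharge contacts are not tied to side effects. If collection stops at discharge, the arm discharged sooner can show fewer side effects with no true difference.

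Under the stated assumptions, the false ratio runs from about 0.54 (discharge HR 3.0, events to day 21) to 0.93 (HR 1.5, events in days 0-6 only). Its size depends on how far stay differs between arms and on when events occur, and the protocol gives figures for neither.

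A reader might infer more: that side effects are collected only in hospital, that interferon will therefore look safer, and that 42% vs 22% is the expected distortion. The documents do not support this. They name no setting and do not exclude side effects from the remote contacts. They assume no hazard ratio for discharge. The 42% vs 22% figure also needs a constant event rate to day 21.

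**What to change.** - **Safety Assessments:** define side-effect frequency as patients with at least one event from first dose to day 21 in every arm, whether or not still in hospital. Day 21 is already the limit for mortality and new ventilation in the Secondary Outcomes section.
- **Secondary Outcomes:** add a side-effect question to the remote contacts already planned for discharged patients.
- **Reporting:** give days observed by arm, and compare laboratory events, which need the patient on site, over a common early in-hospital period.
- **Oral course:** the lopinavir/ritonavir durations in the General and Study Drugs sections differ and must be reconciled, so that it is clear how much of the course the window covers.

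The cost is a sentence in each of the two sections and one question per contact, with no change to sample size or treatment. The downside is that events after discharge will be self-reported and less detailed than those seen on the ward.

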## **Efficacy Assessments**

**Study Outcomes**

**Primary Outcome:**

Our primary outcome measure will be TTCI, defined as the time from enrollment to discharge from the hospital or a decline of two steps on the seven-step ordinal scale; Which so ever came first. Originally introduced by Beigel and colleagues in a posthoc analysis of an influenza study as a six-step ordinal scale, and currently recommended by the WHO R&D Blueprint Team (Accessed May 15, 2020, at https://www.who.int/teams/blueprint/covid-19.) for COVID-19 studies as a nine- step ordinal scale, the utilized seven-step ordinal scale consists of the subsequent categories: (I) Not hospitalized, and has no activity limitations; (II) Not hospitalized, but has activity limitations; (III) Hospitalized, but does not need any supplemental oxygen; (IV) Hospitalized, and needs supplemental oxygen; (V) Hospitalized, and needs either High-Flow Nasal Cannula (HFNC) or non-invasive ventilation; (VI) Hospitalized, and needs invasive ventilation; and (VII) Dead (9).

**Secondary Outcomes:**

Secondary outcomes include mortality from the date of randomization until day 21, by which all of the patients will have at least one of the following outcomes: 1) A decline of two steps on the seven-step ordinal scale, 2) Hospital discharge or 3) Death; SpO2 improvement defined as the difference between the last and the first recorded measurement during the hospitalization, using pulse-oximetry; length of stay in the hospital until the date of discharge from hospital or death from any cause, whichsoever came first; incidence of new mechanical ventilation uses from the date of randomization until day 21. Follow-ups of discharged patients will be done utilizing telemedicine visits, online, or over the telephone.

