## **Statistical Methods**

Statistical analysis will be performed by R version 3.6.1 software. The total sample size was calculated according to the Latouche and colleagues approach for estimating sample size in survival analysis with 80% power, alpha=0.05, Hazard Ratio (HR) of 3.0 (as the ratio of the hazard rates of time to clinical improvement (TTCI) corresponding to the intervention group compared to the control group) and assuming that 80% of patients would reach the primary outcome (10). The calculations will be carried out using Package ‘powerSurvEpi’ in R and accounted for a dropout

rate of 15%. Overall 60 patients, will be needed for the study, 20 for each arm.

Frequency rates and percentages will be used for categorical variables, and Interquartile Ranges (IQRs) and median will be used for continuous variables. Kruskal-Wallis test will be used for comparing the continuous variables. The Wilcoxon signed-rank test will compare the before and after intervention effects. Moreover, Chi-Square test will compare the frequency of categorical variables. We will use Kaplan–Meier to analyze the TTCI (compared with a log-rank test).

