## **Inclusion Criteria**

- Age ≥ 18
- COVID-19 Confirmed Cases by Means of RT-PCR
- Oxygen saturation (SPO2) ≤ 93% OR respiratory rate ≥ 24
- At least one of the following: Calibrated contactless infrared forehead thermometry temperature of ≥37.8, cough, sputum production, nasal discharge, myalgia, headache or fatigue on admission.
- Time of onset of the symptoms should be acute (Days ≤ 14)

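### SpO2 improvement is last minus first in-hospital reading, with no condition on oxygen support, day, randomisation or death, and the planned before-after test cannot show a treatment effect

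*Protocol*

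**What the plan says.** The Protocol's Secondary Outcomes section (under Efficacy Assessments) defines "SpO2 improvement defined as the difference between the last and the first recorded measurement during the hospitalization, using pulse-oximetry". The Protocol Summary has a near-equivalent: "SpO2 Improvement between the last and first day of hospitalization, using pulse-oximetry". Neither states what oxygen support the patient is on at either reading, a day common to all patients, or what is done when a patient dies.

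Three other parts of the Protocol bear on this:

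- **Care in all arms** (Study Design, General): "All three groups will receive standards of care consisting of the necessary oxygen support, non-invasive, or invasive mechanical ventilation".
- **Entry** (Inclusion Criteria): "Oxygen saturation (SPO2) ≤ 93% OR respiratory rate ≥ 24".
- **Analysis** (Statistical Methods, full section): "Kruskal-Wallis test will be used for comparing the continuous variables", followed by "The Wilcoxon signed-rank test will compare the before and after intervention effects". The second sentence names no variable and does not say that the test is run within each arm.

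The second item under Secondary objectives is comparative: "To determine and compare the average level of oxygen saturation (Sat O2) in three therapeutic arms".

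**The concern.** SpO2 is a value that clinicians hold up with oxygen. Read without the support being given, a higher last value may mean recovery or escalation. The two time points also depend on other outcomes. The last reading falls near discharge in survivors and near death in those who die, so both its timing and its meaning vary with stay and survival. The first reading belongs to the hospital stay, not to the trial.

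Two things are at stake. The between-arm comparison of this outcome could be hard to interpret, losing a real effect or showing a difference that reflects support, stay or deaths. And a paired test labelled as comparing intervention effects could be reported as efficacy when it shows only that patients in an arm had higher readings at the end of their stay than at the start.

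**Working it through.** **1. Definition against planned care.** On the protocol's seven-step scale, category IV is supplemental oxygen and category VI is invasive ventilation. A patient who moves from IV to VI is worse on the primary outcome's own scale. If ventilation raises the SpO2 reading, the same patient scores a positive SpO2 improvement. Nothing in the definition prevents this.

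**2. Baseline.** In the same Secondary Outcomes text, mortality and new ventilation run from randomisation, but SpO2 runs from the first reading of the hospitalisation. A gap between that reading and randomisation is permitted, though the Protocol does not say that one exists.

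**3. Number per arm.** The Protocol gives no planning figure for SpO2. Its stated size of 60 reproduces for the primary outcome, taking alpha as two-sided:

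- events for one pairwise comparison = (1.96 + 0.84)² / (0.25 × (ln 3)²) = 26.01, rounded up to 27
- 26.01 / 0.80 / 0.85 = 38.3, and 27 / 0.80 / 0.85 = 39.7
- hence 39 to 40 for two arms, 20 per arm and 60 in all

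So n = 20 per arm, or 20 × 0.85 = 17 after the planned dropout.

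**4. Behaviour of the two tests with no treatment effect.** All SpO2 inputs are assumptions, because the Protocol gives none: true SpO2 mean 90 (SD 4), measurement SD 2 per reading, first reading 93% or less, values capped at 100, and the same natural change in all arms. There were 3,000 simulated trials per row.

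| Natural rise (SD) | Signed-rank significant rise in one arm, n = 20 | Same, n = 17 | Kruskal-Wallis on change, n = 20 |
|---|---|---|---|
| 0 (0) | 7.1% | 7.6% | 4.9% |
| 0 (3) | 5.4% | 5.2% | 5.1% |
| 1 (3) | 28% | 23% | 4.6% |
| 2 (3) | 69% | 60% | 5.1% |
| 3 (4) | 81% | 74% | 4.7% |
| 5 (4) | 99.7% | 98.5% | 4.4% |

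With n = 20, all three arms, control included, were significant together in 30% of trials at a 2-point rise and 99% at 5 points.

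A closed-form check uses power ≈ Φ(d × √(0.955n) − 1.96), where d is mean change divided by its SD. For the 2-point row the simulated mean change is 2.37 and the SD is about √(3² + 2² + 2²) = 4.12, so d = 0.57. Then 0.57 × √19.1 − 1.96 = 0.53, and Φ gives about 70%, against 69% simulated.

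With zero natural rise and selection on the first reading, the mean change is about 0.4 point. That is the whole contribution of regression to the mean under these SDs.

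**5. Dilution of the between-arm comparison.** Assume a first SpO2 of about 89 (SD 4), a natural rise of 3 (SD 4), a true benefit of 3 points in both interferon arms and 20 per arm. Kruskal-Wallis detects the benefit in about 61% of trials when readings are on equal support. If patients who would be below 92% are brought to about 94% by oxygen, it detects the benefit in about 15%. These inputs are illustrative only.

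**The case against.** The strongest reply is that the plan does include a controlled comparison. Kruskal-Wallis is stated for continuous variables in the sentence just before the signed-rank test, and the SpO2 objective is set across three arms. Recovery common to all arms creates no false difference there, as the last column of the table shows. This stands. A reader might infer that the plan tests SpO2 only before-after, so that the outcome will show benefit without any effect. The documents do not support that reading.

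Four further limits also stand:

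- The link from the signed-rank test to SpO2 within arms is an inference. It is reasonable, because SpO2 is the only listed secondary outcome defined as a change, but the Protocol does not state it.
- The signed-rank percentages are the power of a paired test to detect an assumed real rise. They are not false-positive rates of the trial's treatment comparison.
- It is tempting to blame regression to the mean or change before randomisation. The first is small under the assumed SDs, and does not arise on SpO2 for patients who enter on respiratory rate alone. The second is possible but not shown, and between randomised arms it would mainly add noise.
- Oxygen need and death are captured by the primary scale and by separate secondary outcomes, which confines the harm to one secondary outcome.

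The reply does not repair the score itself, since Kruskal-Wallis would be run on the same last-minus-first values. Nor is this only a detail for an unseen SAP, because the Protocol itself fixes the two time points.

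**Conclusion.** The point holds for the outcome definition and for the use of a before-after test as evidence of effect. As written, the definition can score escalation as improvement. It can also dilute or bias the between-arm comparison if support, stay or deaths differ by arm. The direction of any bias cannot be told from the documents. The dilution example (61% to 15%) shows that it could be large, but rests wholly on assumed values.

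The signed-rank test, if applied to SpO2 as seems intended, would be significant in about 28% to over 99% of arms of 20 for assumed natural rises of 1 to 5 points, and in 5% to 7% with no rise. It therefore says little about interferon. The planned Kruskal-Wallis test does not share that fault when recovery is equal across arms. This is a secondary outcome, so the change is advisable and does not threaten the primary analysis.

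**What to change.** In Secondary Outcomes, and to match in the Protocol Summary:

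1. Take as baseline the last SpO2 at or before randomisation, and as the outcome the value on one prespecified day common to all patients.
2. Record the oxygen support with each reading and account for it in the analysis, for example by SpO2/FiO2 or by stating the oxygen condition to which the outcome refers. This concerns recording and analysis only, not the oxygen that patients receive.
3. State how patients who die or are discharged before that day are scored.

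In Statistical Methods:

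4. Base inference on the between-arm comparison only, preferably adjusted for baseline SpO2.
5. Remove the signed-rank test as a test of intervention effect and report before-after changes by arm descriptively.

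The cost is about one extra field on the daily vital-signs record already planned under Safety Assessments. FiO2 on nasal oxygen is approximate, and the rule for deaths and early discharges involves a choice that should be written down before the data are seen. A full rank composite of SpO2/FiO2, death and discharge is one option, but it would be a new endpoint overlapping the primary outcome and is not needed to resolve this point.
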